### Primary outcomes

All assessments will be performed by a trained pediatric physiotherapist who will evaluate all participants at the site. The therapist will be thoroughly trained during the site initiation visit and provided with an illustrated guidebook to ensure consistency across sites. The assessing therapist will be blinded to the group assignments.

Gross Motor Function Measure-88 (GMFM88): GMFM88 is a standardized observational instrument designed and validated to measure change in gross motor function over time in children with CP using a 4-point Likert scale for 88 items across five dimensions: (a) lying and rolling, (b) sitting, (c) crawling and kneeling, (d) standing, and (e) walking, running, and jumping. The participant will complete a number of gross motor activities, depending on the age and ability (Russell et al., 2002; Ko and Kim, 2013). The GMFM88 item scores will be summed to calculate raw and percent scores for each of the five dimensions and a total GMFM88 score. Participants will be designated as responders if they demonstrate at least 5-point increase in GMFM88 score from baseline, as assessed at the end of the 8-weeks (visit 17). Participants will be designated as non-responders if this criterion is not met. The criteria for success are defined as at least 50% of the children in the therapeutic group being classified as a responder.

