## Trial objectives

The primary objective is to assess the safety and efficacy of 8 weeks of SCiP™ therapy during ABNT compared to sham (inactive) neuromodulation during ABNT in improving voluntary sensorimotor function measured on the GMFM88 scale in children with CP. The secondary objective is to assess the safety and efficacy of short-term (8 weeks) vs. long-term (16 weeks) SCiP™ in conjunction with ABNT in improving voluntary sensorimotor function (GMFM88 score). We hypothesize that children who undergo SCiP™ neuromodulation therapy in conjunction with ABNT will demonstrate a statistically greater improvement in voluntary sensorimotor function as assessed by GMFM88 scores, compared to subjects undergoing sham modality in conjunction with ABNT. The proposed clinical trial was discussed with the US FDA via a virtual sprint discussion owing to the breakthrough device status; and SpineX and the agency have reached an alignment on the clinical trial design, primary and secondary outcomes, sample size and safety outcomes.

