### Sample size and power

We assume a true sham responder rate of 0.22 or less, and a treatment responder rate of 0.68 or higher, based upon pilot study observations and assuming 10% attrition of participants during the study. Thus, a sample size of 60 will support 80% power to distinguish between the arms, in a two-sided exact test at the 0.05 significance level. Considering the heterogeneity of prospective participants, proposed sample size of 60 participants (30 per arm) will ensure 80% power for primary endpoint comparison, allowing for precise estimation of responder rates in different demographic subpopulations. Assuming 25% attrition rate of participants in screening based on pilot study, the required number of participants to be screened is 80. The proposed sample size is consistent with other similar studies (NCT05020834, NCT04725019, NCT05154253, NCT05351138).

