### Statistical analysis

Randomization will be stratified by age and GMFCS level. Demographics and baseline characteristics will be summarized for all patients using summary statistics for continuous variables (number of patients, mean, standard deviation, median, minimum and maximum) and using group frequencies or percentages for discrete variables. Study arms will be compared with respect to these characteristics using two-sample t-tests, binomial-based tests, chi-squared tests, or nonparametric alternatives. The primary endpoint, the GMFM88 score responder rate (i.e., >5-point increase from baseline), will be estimated and compared between groups using a two-sided chi-squared test at the 0.05 significance level. In the event of small expected cell sizes (e.g., <5), an exact test will be used. If baseline characteristics differ between study arms, logistic regression will be employed, with those characteristics, as well as stratification factors, as covariates. The secondary endpoint, the Modified Ashworth Scale (MAS) responder rate (i.e., > 0.45 change from baseline), will also be estimated and compared between treatment arms using a two-sided chi-squared test. Change-from-baseline to Phase I evaluation in MAS, GMFM88 Dimension A, B, C, D, and E, PEDI-CAT, and 10MWT (GMFCS levels I, II, and III only) will be computed for each participant as the difference between the two measurements; these will be compared between treatment groups using two-sided, two-sample *t*-tests at the 0.05 significance level. Data transformations or nonparametric methods will be substituted if the data are not found to be normally distributed. As an additional ancillary analysis, the Phase I primary, secondary, and ancillary efficacy endpoints will be compared between study arms using logistic regression, analysis of variance, or other statistical modeling appropriate to the endpoint, with stratification factors and other baseline and demographic factors as covariates. Interaction testing and subgroup analyses will be employed to investigate consistency or heterogeneity of treatment effect across subgroups based upon age, gender, race, ethnicity, clinical site, underlying condition, and/or other baseline and demographic factors. The ancillary endpoints will also be estimated in the treatment group as change from baseline to the final evaluation visit (post 8-or 16-week, visit 34), and in the control group as change from the Phase I post 8-week evaluation to the final evaluation visit (post 8 or 16-week, visit 34), with 95% confidence intervals (CI). Similar methods will be employed to characterize change from baseline (as well as change from final evaluation visit) through the follow-up phase (week 24). Safety analyses will establish frequencies of adverse events, in total and by type, along with 90% CIs. Analyses will be conducted under intent-to-treat principles. The extent of missing data will be evaluated and addressed using multiple imputation (subject to evidence supporting an assumption of Missing at Random) together with sensitivity analyses.

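### The only stated success rule is at least 50% responders in the SCiP arm alone; it can be met without beating sham, and nothing reconciles it with the sham-controlled primary test

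*Protocol article*

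**What the plan says.** Under Primary outcomes, the protocol article defines a responder by the gain in GMFM88 from baseline to visit 17 and then sets the rule for the trial: "The criteria for success are defined as at least 50% of the children in the therapeutic group being classified as a responder". This is the only success criterion in the document. It names one arm, a point estimate and a threshold. It gives no comparison, confidence bound or test.

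The rest of the primary question is comparative:

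- Trial objectives: SCiP is assessed "compared to sham (inactive) neuromodulation during ABNT in improving voluntary sensorimotor function measured on the GMFM88 scale", and the hypothesis is that treated children "will demonstrate a statistically greater improvement in voluntary sensorimotor function as assessed by GMFM88 scores, compared to subjects undergoing sham modality".
- Sample size and power: "We assume a true sham responder rate of 0.22 or less, and a treatment responder rate of 0.68 or higher". The 60 participants are chosen to distinguish the two arms.
- Statistical analysis: the responder rates "will be estimated and compared between groups using a two-sided chi-squared test at the 0.05 significance level". The fallback is also a between-arm test: "In the event of small expected cell sizes (e.g., <5), an exact test will be used".

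No section says whether the 50% threshold applies together with this test, instead of it, or only as a benchmark.

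**The concern.** Both arms receive the same ABNT twice a week, and the protocol itself allows for responders on sham. A responder rate in the SCiP arm alone cannot separate the effect of stimulation from that of ABNT, normal development or repeated testing. The randomized sham arm is there to make that separation, and the success rule does not use it.

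The plan therefore holds two rules for the same endpoint that can give different answers. If they disagree, the document does not say which one stands, and a choice made after the results are known would be hard to defend. The serious direction is a declared success without evidence that SCiP did better than sham.

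**Working it through.** **Inputs.** From the protocol article: 30 evaluable children per arm (Study population and recruitment); planning responder rates of 0.68 for SCiP and 0.22 for sham (Sample size and power); two-sided chi-squared test at 0.05, with an exact test if expected cells are below 5 (Statistical analysis); success at 50% or more of the SCiP arm, which is 15 or more of 30 (Primary outcomes). Every other responder rate below is an assumption, used to show the range.

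**The plan's own figure.** The article states 80% power for a two-sided exact test with 60 participants. Exact enumeration of two binomials at 0.68 versus 0.22 gives 93.7% for Fisher's test at 30 per arm and 89.5% at 27 per arm, that is, after 10% attrition. The stated 80% is not reproduced, but it errs on the cautious side and does not affect this point.

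**Step 1: can the rule be met without beating sham?** Take the smallest passing result, 15/30 on SCiP. With pooled rate p, z = (difference in rates) / √[p(1−p)(2/30)].

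- Sham 7/30: p = 22/60 = 0.3667; difference 8/30 = 0.2667; standard error √(0.3667 × 0.6333 × 0.0667) = 0.1244; z = 2.14; p-value 0.032.
- Sham 8/30: p = 23/60 = 0.3833; difference 7/30 = 0.2333; standard error 0.1255; z = 1.86; p-value 0.063.
- Sham 15/30: difference 0; p-value 1.0. The rule is still met.

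The smallest expected cell counts are 11, 11.5 and 15, so chi-squared is the planned test in each case. With 15/30 on SCiP, any sham count of 8 or more leaves the rule met without a significant difference in favour of SCiP.

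**Step 2: how often does an ineffective device meet the rule?** If both arms share a true responder rate r, the rule is met with probability P(X ≥ 15), X ~ Binomial(30, r). The right-hand column is the chance that the planned test is significant in favour of SCiP, from enumeration of all 31 × 31 outcomes with Fisher's test substituted when an expected cell is below 5.

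| Common rate r | Source | Rule met | Planned test favours SCiP |
|---|---|---|---|
| 0.22 | planned sham rate | 0.07% | 2.3% |
| 0.30 | assumed | 1.7% | 2.4% |
| 0.35 | assumed | 6.5% | 2.4% |
| 0.40 | assumed | 17.5% | 2.4% |
| 0.50 | assumed | 57.2% | 2.6% |

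Up to a common rate of 0.30 the rule is stricter than the test. By 0.35 it is looser, and from 0.40 the gap is wide.

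**Step 3: the reverse conflict.** 14/30 (46.7%) versus 5/30 (16.7%) fails the rule. Here p = 19/60 = 0.3167, the difference is 0.30, the standard error is 0.1201, z = 2.50 and the chi-squared p-value is 0.012. Fisher's test gives 0.025. Either way the comparison is significant and the rule says failure.

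**Step 4: at the planning rates, 0.68 versus 0.22.** The rule is met in 98.8% of trials, the planned test favours SCiP in 96.4%, and both hold in 95.9%. They disagree in about 3.4%: 2.9% with the rule met but no significance, 0.5% the reverse.

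**The case against.** The strongest reply is that the inference is comparative where it counts. The hypothesis, the sizing and the primary-endpoint analysis are all against sham, and the type I error of that test is unaffected by a sentence placed after the description of the instrument. On that view the 50% figure is a clinical benchmark beside the test. The article also condenses a fuller protocol, and possibly an SAP, that may set out a decision rule. This reading is plausible, but the sentence presents itself as the definition of success and nothing attaches it to the test. The point concerns a rule that is stated, not one left for another document.

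The second reply concerns size, and much of it stands. A reader might infer from the 57% that the trial runs a large risk of false success. The document does not support that: 57% needs half of the children in both arms to respond, while the protocol plans on a sham rate of 0.22 or less, where the figure is 0.07%. What remains is that 0.22 is itself an assumption, and a concurrent control exists so that the conclusion need not depend on it.

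A reader might also infer that the plan is wrong because a superior device could miss 50%. That is not an error in itself. A minimum response rate on top of superiority is a legitimate choice, provided it is stated as such. What is at fault is that its status is not stated.

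**Conclusion.** The point holds as a conflict within the document: the one stated success criterion looks at the SCiP arm alone, the trial is designed and tested against sham, and no text reconciles them. The core defect is that success can be met without beating sham.

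Its practical size depends on the sham responder rate under ABNT. If that rate is near the planned 0.22, or even 0.30, an ineffective device would rarely reach 50%. If it is 0.35 or more, the rule passes an ineffective device more often than the planned test does: 6.5% at 0.35 and 17.5% at 0.40, against 2.4%. These higher rates are assumptions, and nothing in the document shows that they will occur. All figures assume 30 evaluable children per arm.

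The evidence does not show that the planned test lacks type I error control, or that the sponsor would claim success without a significant difference. It shows only that the written rule would permit such a claim.

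**What to change.** Replace the success sentence under Primary outcomes with a comparative one: the trial succeeds if the Phase I responder rate is significantly higher with SCiP than with sham, by the test in Statistical analysis, two-sided at 0.05, with the difference in favour of SCiP. Then give the 50% threshold one of two explicit roles:

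- a descriptive benchmark, reported but not decisive; or
- an additional condition that must hold together with the significant test, accepting that a significant result such as 14/30 versus 5/30 then misses success.

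Either role settles which rule decides. Any SAP should carry the same wording, and the change should be made before unblinding.

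The cost is one sentence and no participants. At the planning rates, requiring both conditions lowers power from 96.4% to 95.9%.

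The responder cut should be aligned in the same edit, because it determines who counts toward either rule. Primary outcomes has "Participants will be designated as responders if they demonstrate at least 5-point increase in GMFM88 score from baseline", while Statistical analysis requires a gain strictly above 5 points.

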### Secondary outcomes

Modified Ashworth Scale (MAS): This scale is designed to measure muscle tone, generally defined as the resistance of muscle as it is being passively lengthened or stretched (Bohannon and Smith, 1987). The muscle groups tested in the upper and lower limbs will be averaged to get a total score. The participant will be placed in the supine position. When testing a muscle that primarily flexes, the joint will be placed in a maximally flexed position and moved to a position of maximal extension over a 1 s count of “one thousand one.” When testing a muscle that primarily extends a joint, the joint will be placed in a maximally extended position and moved to a position of maximal flexion over one second (count “one thousand one”), while grading the ability of the joint to move through the passive range of motion relative to the patient’s muscle tone. The scale is graded as follows:

0: No increase in muscle tone.

1: Slight increase in muscle tone, with a catch and release or minimal resistance at the end of the range of motion when an affected part is flexed or extended.

1+: Slight increase in muscle tone, manifested as a catch, followed by minimal resistance through the remainder (less than half) of the range of motion.

2: A marked increase in muscle tone throughout most of the range of motion, but affected part(s) are still easily moved.

3: Considerable increase in muscle tone, passive movement is difficult.

4: Affected part is rigid in flexion or extension.

### Ancillary outcomes

10 m walk test (10mWT): The 10mWT is used to assess walking speed in meters/s (m/s) over a short distance (Jackson et al., 2008; Bahrami et al., 2017). The start and end point of a clear 10 m walkway will be marked. Additional marks will be added at 2 m and 8 m (identifying the central 6 m to be timed). The total time taken to ambulate 6 m is recorded in m/s. The test will not involve the use of any assisted devices.

Pediatric Evaluation of Disability Inventory Computer Adaptive Test (PEDI-CAT): PEDI-CAT contains item bank of 276 functional activities acquired throughout infancy, childhood and young adulthood (Haley et al., 2011). It will be completed by the parents/caregivers of study participants. The PEDI-CAT measures function in four domains: (1) Daily Activities; (2) Mobility; (3) Social/Cognitive, and (4) Responsibility. The items enable clinicians to construct a description of a child’s current functional status or progress in acquiring routine functional skills.

Gross Motor Function Measure-66 (GMFM66): The GMFM66 consists of a subset of the original 88 items of the GMFM88 divided into five dimensions: Lying and rolling (4 items), sitting (15 items), crawling and kneeling (10 items), standing (13 items), and walking, running, and jumping (24 items) (Beckers and Bastiaenen, 2015). The GMFM66 was developed to improve the interpretability and clinical utility of the GMFM88. A computer program, the Gross Motor Ability Estimator will be used.

Pain Assessment Instrument for CP (PAICP): Nonverbal scales for pain assessment are necessary for CP patients due to their inability to express pain verbally, visual and cognitive impairment. The PAICP instrument consists of 6 drawings of daily situations that are usually not painful and 6 that usually are painful. Patients rate the pain associated with each activity using a Faces Pain Scale (Boldingh et al., 2004).

Vitals including Heart Rate, Blood Pressure and Oxygen Saturation: Vitals will be measured at every visit using Carescape V100 vital signs monitor (GE Healthcare, WI, United States).

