### Study population and recruitment

Up to 80 participants (ages ≥2 and ≤ 13 years), diagnosed with CP, spastic diplegia, spastic hemiplegia or spastic quadriplegia, and GMFCS Level I-V will be consented to achieve a minimum of 60 evaluable datasets (30 treatment, 30 control) at the primary Phase I endpoint of 8 weeks (see statistical analysis for sample size calculation). The inclusion/exclusion criteria are described in Supplementary Table S1.

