### Randomization and blinding

Participants will be randomized into a treatment (SCiP™) arm and control (sham) arm in a 1:1 ratio. A block randomization technique will be employed, and randomization will be stratified by age (2–7 and 8–13) and GMFCS level (levels stratified as I + II + III & IV + V; ambulatory and non-ambulatory groups). All participants and the clinicians administering the assessment will be blinded to the initial group assignment. The sham device will be physically identical and intensity on the LCD display will be shielded from the participants. At Phase I primary evaluations, participants will be asked what treatment they believe they received using the Bang blinding index (Bang et al., 2004). Participants will not be blinded during the Phase II, open label extension during which all subjects will receive SCiP™ treatment.

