**Figure 2 fig2:**
[figure not shown]
Depiction of wearability and form-factor of Spinal Cord Innovation in Pediatrics (SCiP™) unit and electrodes placement on a child.

Participants randomized to the therapeutic group will receive transcutaneous neuromodulation via SCiP™ device. The motor threshold will be determined by the therapist via a visible motor contraction of paraspinal, abdominal, upper or lower extremity muscles induced by the stimulation. During training, a sub-motor threshold intensity will be used to ensure no motor evoked responses are generated (muscle contractions) and that the stimulation does not result in pain or discomfort. The stimulation will begin at 0 mA and will be increased by 1 mA every 10 s within sub-motor threshold intensity. Intensities over the C5-6 spine will range between 6 and 20 mA and over the T11-12 between 5 and 16 mA based on the activity being performed and subject-specific responsiveness. Initial stimulation amplitude will be set when the participant voluntarily attempts to extend the cervical or thoracic regions while in a seated position. Based on our preliminary observations, the amplitude will be lowered by 1–2 mA during activities involving sitting, rolling etc., and increased by 2–4 mA during standing and stepping. The intensities will be modulated ±2 mA based on the functional performance of the participant and the sensory perception skills of the therapist during the task.

Participants randomized into the sham group will not receive active electrical stimulation. However, to ensure sufficient blinding, during each session, with the child in a seated position, stimulation will be delivered at C5-6 and T11-12 at an intensity of 1 mA for a period of 1 min. After 1 min, the stimulation will be automatically decreased to 0 mA, however, the SCiP™ device will continue to make a beeping sound mimicking a therapeutic stimulation session. To ensure consistency across multiple sites, all site personnel will be thoroughly trained and provided with a written guidebook.

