
## Data management and safety

Parents and/or legal guardians of all eligible participants will be invited to discuss the protocol and its risks and benefits with the site Principal Investigator (PI). Parents and/or legal guardians of potential participants will be given at least 72 h and will be encouraged to read the informed consent, and discuss the study with their child, physician, family, and friends, before signing the IRB-approved informed consent. The informed consent forms will be written in a language understood by an eighth-grade student and will contain information on all outcomes as well as PI’s contact information. IRB-approved age-appropriate assent forms will be provided to minors, based on considerations such as the age, maturity, and degree of literacy. Assent from pre/non-literate children will be obtained in accordance with local IRB requirements.

The original signed informed consent (and assent, if applicable) and two copies will be kept in the PI’s office. No participant will be allowed to enroll without being examined by site PI. The participants will be monitored closely to assess for evidence of complication from experimental protocol. The data monitor, clinical research operations team and medical monitor will closely monitor the participants in regards to the procedures and will be available for consultation.

During training, every participant will be slowly acclimated to the treadmill and other devices. Vitals will be monitored (blood pressure, oxygen saturation, heart rate, pain scores) at each session. Stimulation will be stopped in case of an adverse event during and the participant will receive appropriate standard of care treatment. Before and after every session, a physical therapist will examine the participant’s skin for irritations and abrasions. If skin irritations or abrasions are caused by the recording electrodes or hand placements of trainers, electrode and hand placement will be modified. Furthermore, the therapist will monitor the participant’s skin and muscle for signs of muscle strain, joint sprain, and skin irritation (e.g., temperature and redness). The therapist will assess the appropriate lower extremity parameters and monitor manual assistance by trainers to avoid joint sprain. The physical therapist or trained staff member will stretch the muscles of the participants before and after each training session to prevent injury. PAICP will be completed at every session to monitor for pain signs.

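### The only pain instrument described for every session, the PAICP, asks about pictured daily situations rather than the stimulation session, and relies on self-report from age 2

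*Protocol article*

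**What the plan says.** All references are to the protocol article.

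- **Purpose and frequency.** Data management and safety states: "PAICP will be completed at every session to monitor for pain signs". Table 1 agrees, marking the PAICP at screening, baseline, all treatment visits and all evaluation visits.
- **Content.** Ancillary outcomes states: "The PAICP instrument consists of 6 drawings of daily situations that are usually not painful and 6 that usually are painful".
- **Rater.** The next sentence there reads: "Patients rate the pain associated with each activity using a Faces Pain Scale". The same section gives the PEDI-CAT to parents or caregivers.
- **Rationale.** The reason given for the tool is: "Nonverbal scales for pain assessment are necessary for CP patients due to their inability to express pain verbally, visual and cognitive impairment".
- **Population.** Study population and recruitment covers ages 2 to 13 and all five GMFCS levels. Under Randomization and blinding, ages 2–7 form one of the two age strata.
- **What needs checking.** Intervention requires a sub-motor-threshold intensity and "that the stimulation does not result in pain or discomfort". The same section describes administration as free of pain, and Trial objectives puts safety in the primary objective.

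**The concern.** The stated use of the instrument and its described content do not match. The use is to watch for pain at each stimulation session. The content is how painful a set of pictured everyday situations is. A child who found the electrodes painful could give the same ratings as on a day without pain, because no described item asks about the electrodes or the session.

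The rater is a second difficulty. The article chooses the scale because children may not see well, reason well or speak about pain, then describes a task that needs the child to view drawings and pick a face. For a two-year-old, or a child with the impairments the article names, it is not clear who answers.

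At stake is the evidence for painless stimulation. Phase I is the only blinded, sham-controlled period. If the structured instrument is not aimed at session pain, similar PAICP scores in the two arms would say little about whether active stimulation hurts more than sham.

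**Working it through.** The article gives no figure to reproduce. The check sets its statements side by side.

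**1. Content.** 6 drawings of usually painless situations + 6 of usually painful ones = 12 items, all described as daily situations. None is described as concerning stimulation or the session. The article does not list the drawings one by one, so this is a reading of the category it gives.

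**2. Volume.** Phase I has 16 treatment visits (Table 1), and 60 evaluable children are planned. At full attendance, 16 × 60 = 960 session administrations. This number describes scheduling and is not a measure of harm.

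**3. Rater against population.** The patient rates. Enrolment starts at age 2, and the consent text in Data management and safety expects some children who cannot read. GMFCS grades motor function, so levels IV–V do not by themselves show that a child cannot self-rate. Eligibility is in Supplementary Table S1, which is not shown, and no age distribution or completion rate is given. The share unable to self-rate therefore cannot be derived.

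**4. Other routes by which session pain could be recorded.**

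| Route | Where | What it adds | Limit |
|---|---|---|---|
| Pain scores listed with the vitals at each session | Data management and safety | A per-session entry in both arms | Scale, question and rater not defined; may simply be the PAICP |
| Adverse events at Visits 1–16 and 18–33 | Table 1 | A reporting route at every treatment visit | Depends on a child saying so or an adult noticing |
| Pain around the stimulation site as an anticipated event | Table 3 | Names the event of interest | A listed event, not a standard question |
| Skin examination before and after each session | Data management and safety | Visible irritation or abrasion | Shows signs on the skin, not felt pain |

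**5. Why comparability between arms matters.** Under Intervention, sham is 1 mA for 1 minute and then 0 mA, while active ranges are 6–20 mA at C5-6 and 5–16 mA at T11-12. Any excess pain from stimulation should appear as an arm difference during Visits 1–16. In Phase II every child receives active stimulation, open label, so that contrast is gone. Randomization and blinding states blinding for participants and assessing clinicians and shields the display from participants. The treating therapist finds the motor threshold and adjusts intensity. If pain reports depend on what that therapist notices, ascertainment may differ by arm; a fixed question asked of everyone reduces that risk.

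**The case against.** The strongest reply is that the PAICP is neither the only route nor the safety endpoint. Statistical analysis bases safety on adverse event frequencies, in total and by type, with 90% confidence intervals. Stimulation-site pain is an anticipated event, adverse events are collected at every treatment visit, and pain scores are listed with the vitals. The PAICP is an ancillary outcome and is not among the measures named for the change-from-baseline t-tests. All of this stands. A reader might infer that stimulation pain will go unrecorded; the documents do not support that.

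A reader might also infer that many enrolled children cannot complete the PAICP. Enrolment from age 2 makes the worry reasonable, but the documents give no number, and the eligibility table might contain a communication or cognitive criterion. That stronger reading is not supported either.

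A third reply is that an article condenses: rules for helping the child or using a proxy may be in the full protocol or the site guidebook. This has force on the proxy question, and the point should not rest on silence alone. It has less force on the target of measurement, because the article itself states the instrument, its content, its rater, its frequency and its purpose, and those statements do not fit together.

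Finally, taking the PAICP out of the treatment sessions would be a matter of preference. That also stands; the gain comes from adding a direct question.

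**Conclusion.** The point holds in a limited form. As described, the named per-session pain instrument measures pain in pictured daily situations and depends on self-report from age 2, which suits neither its stated monitoring purpose nor the article's own reason for choosing it. Structured, arm-comparable capture of stimulation pain is weak and falls back on adverse event reporting and an undefined pain-scores entry.

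The size cannot be put as a number of children affected or events missed. What can be said is that none of the 12 items is described as asking about the session. This assumes that the article's summary of the PAICP is accurate and that the pain-scores entry is not already a separate, defined session-pain question. If it is, stating so would settle most of the point. The efficacy analyses are not affected.

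**What to change.** Define the pain-scores entry in Data management and safety as one question on pain during this session:

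- Ask it with the same wording and at the same moment of every session in both arms.
- Let the child rate where able, and otherwise the caregiver. Fix the rater type for each child at Visit 0 and record it.
- Where a caregiver rates, keep that person unaware of the arm through Visit 17. The article states blinding for participants and assessors but does not mention caregivers.
- Summarise the ratings by arm over Visits 1–16, next to the adverse event frequencies, and show them by rater type.
- State in the same place who completes the PAICP when the child cannot.

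The PAICP schedule in Table 1 can stay; fewer session administrations would be optional. The cost is one CRF item and a short addition to the site guidebook. The downside is that proxy ratings are less direct than self-report. Fixing the rater type keeps each child's series on one kind of rater but does not remove that limitation. The change concerns measurement only and leaves stimulation and its management as written.
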